## Abstract

**Background:**

Use of information campaigns and educational interventions directed to citizens and supported by physicians, aimed at promoting the appropriate use of medicines, have been evaluated by several studies with conflicting results. These interventions are potentially relevant, favouring the reduction of unnecessary use of medicines and related risks. Several studies have specifically evaluated the promotion of the appropriate use of antibiotics in adults and children, with variable results. A controlled study is proposed to evaluate the feasibility and effectiveness of a multifaceted intervention aimed at reducing antibiotic prescription by increasing awareness on risks of their unnecessary use.

**Methods/design:**

Information will be provided to citizens through several media (posters, local TV, radio and newspapers, video terminals, websites of Local Health Authorities). Brochures with information on expected benefits and risks of antibiotics will be also available, either with direct access in waiting rooms and pharmacies or handed out and mediated by doctors. Physicians and pharmacists will get specific data on local antibiotic resistance. A small group of representative doctors have also actively participated in defining the campaign key messages. A sample of general practitioners and paediatricians will be trained in patient counselling strategies.

The information campaign will be implemented in two Provinces of Emilia-Romagna during the fall-winter season (November 2011-February 2012). Change in the overall prescribing rate of antibiotics (expressed as DDD per 1000 inhabitants/day) in the intervention area will be compared versus other areas in the same Region. Knowledge and attitudes of the general population will be evaluated through a phone and internet survey on a representative sample.

**Discussion:**

While the campaign messages will be mainly directed to the general population, doctors' prescribing will be assessed. The main rationale for this apparent discrepancy lies in the influence patients may have on physicians' prescribing behaviour (directly or indirectly) and in physicians' endorsement of the campaign goals, considering their participation in its design.

This study could observe a reduction lower than 5% in the prescribing rate of antibiotics. Such a reduction would be of public health relevance and would determine average savings of almost twice as much as the campaign costs.

## Background

Use of information campaigns and educational interventions directed to citizens and supported by physicians, aimed at promoting the appropriate use of medicines, have been evaluated by several studies with conflicting results. Evaluating the feasibility and effectiveness of these interventions is relevant, considering the influence citizens may have on physicians' prescribing habits, both directly (when patients request prescription filling) and indirectly (when physicians think their patients expect getting a prescription) [1]. Physicians could also be motivated in their prescribing behaviour by the implementation of information campaigns, especially if their active participation is requested [2]. Analysing population targets, campaign methods and available experiences can provide useful information for planning this kind of intervention, which may determine potentially relevant contributions to public health by reducing unnecessary use of medicines and related risks.

As for population targets: citizens are exposed to several information sources about the effects of medicines, either through traditional media (TV, journals, radio, etc) or through the internet with its constant evolution to more interactive tools (blogs and the many features of web 2.0). These information are often promoted by drug producers: in Europe, direct-to-consumer drug advertising is currently not allowed (although the European Commission is considering a worrisome proposal to relax this ban) [3] but citizens may be exposed to web contents and, above all, to information promoted by people and institutions sponsored by drug companies, also available through traditional media [4]. These circumstances can favour a biased view of benefits and risks of treatments. Information promoted by public health institutions has generally a weaker potential, since resources and planning are most of the times inadequate if compared with commercially oriented information. Adequate planning of public health initiatives and allocation of economic as well as human resources are necessary in order to provide citizens with an evidence-based, unbiased view of benefits and risks of drug treatments, and to favour their appropriate use.

Several studies have shown the potential of mass media on the use of health interventions [5]. Medicines represent a relatively fortunate topic for a public health information campaign: maybe, suggesting to use medicines wisely in view of their benefits and risks can influence behavioural change more than suggesting the adoption of healthy lifestyles, uneasy to practise in spite of their well known benefits.

Aside from the specific topic focused on, many other variables may influence the effectiveness of multifaceted educational campaigns. Defining one or more relevant target audiences and key messages are essential elements. A thorough evaluation of local contexts and a wise mix of information tools is necessary as well, taking lessons from those who do commercial information and advertising. ''Social marketing'' techniques may help the promotion of evidence-based knowledge. This term refers to the application of marketing techniques to the solution of social and health problems [6]. A social marketing approach to evidence-based information could take into account a planning process involving ''consumer'' oriented research, objective setting, identification of barriers and, consequently, of strategies and tools to facilitate the transfer of key messages

As for doctor's role: information campaigns could be more effective if physicians facilitate the transmission of information to their patients [7]. In order this potential to be unfolded, it may be necessary to work on doctors' motivations and skills in better conveying information to their patients, in spending some more time and energy to evaluate patients' expectations, possible obstacles to attitudinal and behavioural changes and eventually to find the right keys motivating them to such changes.

Practicing physicians can also provide substantial help in developing campaign messages, since they are in a relevant position to evaluate comprehensibility and potential effects of specific information in the context of patient expectations in primary care. Such participation can also increase their sense of ownership of the campaign goals and facilitate their endorsement [2], which can ultimately lead to increased attention to appropriate prescribing. Lastly, doctors may be influenced by the awareness that patients could be more informed about (and more sensitive to) the campaign topic [8].

Several studies have evaluated the effects of educational interventions focused on the appropriate use of antibiotics in adults and in children. A Cochrane systematic review, reporting the results of 39 among RCTs and observational studies [9], showed that such interventions can be successful especially when local context and barriers are adequately analyzed and addressed. Specifically, multifaceted interventions involving both physicians and patients/public, using written information material, educational meetings and mass media seem moderately effective, more than single interventions, in decreasing antibiotic prescribing for inappropriate indications (range of absolute differences: 3-33%); only one of these studies, carried out in Finland, showed a reduction in antibiotic resistance (erythromycin resistance was halted in four years). Another systematic review published in 2008, reporting the results of 43 among RCTs and observational studies, showed that educational strategies involving physicians (in particular active education through seminars and visits) and patient education strategies (through written material and mass media) are moderately effective in reducing unnecessary antibiotic use (median absolute difference: 10%) [10]. Several studies evaluating the impact of regional and national information campaigns on antibiotic use are available, carried out especially in Australia [11,12] and the United States [13-15], but also in Europe (for example in France [16]). In selected cases, a favourable cost effectiveness ratio was shown [13]. A recent survey under the auspices of the European Commission revealed that information campaigns may change people's behaviour in terms of antibiotic use: more than one out of 10 people remember to have received information on this issue and are willing not to take antibiotics without talking to a doctor [17]. Definitively, there seems to be room for improving citizens' knowledge about the correct use of antibiotics.

Within a wider project called ProBA project (progetto Bambini Antibiotici), in 2003 the Health Agency of the Emilia-Romagna Region carried out a survey on 633 paediatricians (453 working as family paediatricians and 180 working in hospitals) and 1388 parents, aimed at evaluating the main determinants of antibiotic prescriptions for children [18]. This survey showed that improving paediatricians' and parents' knowledge on benefits and risks of antibiotics, and suggesting that resistance is a problem at the community but also at the individual level, may favour their more appropriate use.

Starting from these considerations and from local and international experiences on educational campaigns, we propose a study to evaluate the feasibility and effectiveness of a multifaceted intervention on antibiotic prescription in the general population, aimed at reducing it by increasing awareness on risk of unnecessary use, thus reducing patients' requests for unnecessary prescription. The specific objectives are:

• primarily, to reduce the overall volume of antibiotic prescription;

• secondarily, to reduce total costs associated to antibiotic prescriptions; to evaluate knowledge, attitudes and reported behaviours of a sample of citizens on benefits and risks of antibiotic use; and to evaluate trends in antibiotic resistance (in a three year period after the intervention) from sputum, throat swab, urine and blood samples

We consider such intervention of high public health relevance, considering the limited development of new antibiotics and the public health threat due to antibiotic resistance, which is in part accounted for antibiotic use in humans. The proposed intervention will involve citizens, general practitioners and paediatricians in two Provinces of Emilia-Romagna. In addition to promoting the appropriate use of antibiotics, this project will help to evaluate the feasibility of carrying out information campaigns on benefits and risks of medicines promoted by Local Health Authorities, with the collaboration of local physicians.

## Methods/design

This study will be a community level, controlled, non randomized trial. An information campaign on benefits and risks of antibiotic use, in general and specifically in upper respiratory infections, will be implemented in the provinces of Modena and Parma, in the Emilia-Romagna region. Regional areas where no campaign will be implemented and no information provided to physicians either will be the control group; the presence of local policies on antibiotics that would possibly alter the comparison with intervention areas will be evaluated immediately before implementing the campaign, so that provinces which may supply misleading data would not be included in the control group. Anyway, prescription of antibiotics in the intervention and control areas shall be similar at baseline (no statistically significant differences).

Considering that the proposed educational intervention will be done at the community level and will be multifaceted using several media, and considering its implementation in only two provinces, we think a randomised design would not add strength to the study validity: in fact, it would be impossible to restrict exposure to half the population and there would be too few units of randomisation. Therefore, we choose a non randomised design which is more feasible given those circumstances.

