### Primary Outcome

Cumulative five-month (November to March) changes in prescribing rates of specific classes of antibiotics in general practice, expressed as DDD per 1000 inhabitants/day.

Data on antibiotic prescriptions (on beta-lactams, cephalosphorins, macrolides, fluoroquinolones, corresponding to J01C, J01D, J01F, J01M atc codes) will be retrieved from regional prescribing databases. They will include NHS prescriptions only from general practitioners (a small part of prescriptions may be made outside NHS on personal prescription books) and will not assess the actual use of antibiotics. In Emilia-Romagna, prescriptions from paediatricians are expressed in pieces and not in DDD, and will be evaluated separately.

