### Sample size calculation

In the first three months of 2011, antibiotic prescribing rate in the provinces chosen as possible intervention areas was 21,1 DDD per 1000 inhabitants/day. Ratio of prescribing rates in intervention vs other Provinces in Emilia-Romagna was 1. Standard deviation of the distribution of antibiotic prescribed by general practitioners was about 3,0 in a 2007 dataset of antibiotic prescriptions in the province of Modena. Assuming that ratio of prescribing rates has not changed, that standard deviation of antibiotic prescription is 6,0 (a very conservative doubled figure compared to the 2007 sample) and that is similar in exposed and not exposed areas, it will be possible to observe tiny reductions of antibiotic prescription, and surely meaningful reductions of at least 3-5%, with alfa = 5% and beta = 10%. Potential average economic savings of such reductions would more than offset the fund received to finance the campaign and would be more than three times the out-of-pocket expenses to implement the campaign.

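### Baseline similarity rests on a non-significant test of level, which can pass gaps of about 60% of the powered effect and does not check pre-campaign trends

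*Protocol article*

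**What the plan says.** The trial is a non-randomised, community-level comparison of two campaign provinces with other areas of the same region. Methods/design sets two conditions on the control group. Provinces with local antibiotic policies that could distort the comparison are left out, which is assessed just before the campaign. In addition, "prescription of antibiotics in the intervention and control areas shall be similar at baseline (no statistically significant differences". The bracketed words are the only definition of similarity. They carry no margin and no condition on trends.

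The section Primary Outcome defines the endpoint as "Cumulative five-month (November to March) changes in prescribing rates of specific classes of antibiotics in general practice".

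The section Sample size calculation gives these planning figures:

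- For January to March 2011, "antibiotic prescribing rate in the provinces chosen as possible intervention areas was 21,1 DDD per 1000 inhabitants/day".
- For the same comparison, "Ratio of prescribing rates in intervention vs other Provinces in Emilia-Romagna was 1".
- On variability between GPs, the article reports: "Standard deviation of the distribution of antibiotic prescribed by general practitioners was about 3,0 in a 2007 dataset".
- For planning it is assumed that "standard deviation of antibiotic prescription is 6,0 (a very conservative doubled figure compared to the 2007 sample".
- The stated aim is to observe "surely meaningful reductions of at least 3-5%, with alfa = 5% and beta = 10" (that is, 90% power). The number of GPs is not given.

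The section Statistical analysis lists time series analysis and, for secondary analyses, regression on baseline prescribing, province and district. It reserves ANCOVA for the primary outcome for the case that baseline imbalances are judged relevant.

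**The concern.** There are two separate problems with the rule.

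**It treats failure to reject as evidence of similarity.** What passes depends on the precision of the test. Few GPs or a large SD make the rule lenient, and many GPs or a small SD make it strict. The size of gap that would matter for this study does not enter the rule at all.

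**It examines level when the endpoint is a change.** A comparison of changes between non-randomised areas is valid if the areas would have moved in parallel without the campaign. Equal levels in one period do not show that. The reported ratio of 1 comes from a single quarter and says nothing about trajectory.

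Followed as written, the rule could accept a control group that is on a different course, or reject one that moves in parallel but differs by a small, stable amount. With a target of only 3-5%, the comparison has little room for a diverging trend.

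**Working it through.** **Inputs from the Sample size calculation.** Baseline rate 21.1; SD 6.0 (planning) or about 3.0 (2007 data); alpha 5%; power 90%; target 3-5%, that is 0.03 × 21.1 = 0.633 to 0.05 × 21.1 = 1.055 DDD per 1000 inhabitants/day.

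**Assumptions.** Alpha is two-sided, since sidedness is not stated. The baseline check uses the GP as unit and the same SD as the main comparison. All GP numbers below are assumed.

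**The plan's own figure.** The 3-5% cannot be reproduced directly, because no number of GPs is stated. Solving backwards with n per arm = 2 × (1.960 + 1.282)² × SD² / d²:

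| SD | for 3% | for 5% |
|---|---|---|
| 6.0 | 1889 per arm | 680 per arm |
| 3.0 | 473 per arm | 170 per arm |

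**Step 1: a ratio that needs no GP numbers.** With SE = SD × √(1/n₁ + 1/n₂):

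- largest gap that passes = 1.960 × SE
- effect detectable with 90% power = (1.960 + 1.282) × SE = 3.242 × SE
- ratio = 1.960 / 3.242 = 0.605, whatever the N, SD or allocation (0.562 if one-sided)

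| Study powered at 90% for | Largest gap that passes (DDD) | As % of 21.1 |
|---|---|---|
| 3% | 0.38 | 1.8% |
| 4% | 0.51 | 2.4% |
| 5% | 0.64 | 3.0% |

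**Step 2: dependence on N and SD.** Largest passing gap as % of 21.1, for assumed GP numbers (intervention vs control):

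| GPs | SD 6.0 | SD 3.0 |
|---|---|---|
| 200 vs 600 | 4.6% | 2.3% |
| 300 vs 900 | 3.7% | 1.9% |
| 600 vs 1800 | 2.6% | 1.3% |
| 1000 vs 3000 | 2.0% | 1.0% |

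An observed gap of 2% (0.02 × 21.1 = 0.42 DDD) passes at SD 3.0 with 200 vs 600 GPs and fails with 600 vs 1800. At 600 vs 1800 it passes with SD 6.0 and fails with SD 3.0. The gap is the same each time; only the precision differs.

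**Step 3: level against change.** Write G for the level gap at baseline and D for the gap in the campaign season. The comparison of changes estimates D − G, so a stable gap (D = G in the absence of effect) cancels. A difference in trend does not cancel, and the rule does not look at it. ANCOVA with slope b estimates D − bG, which differs from the change analysis by (1 − b)G. Unless b = 1 or G = 0, the two analyses give different answers, so the choice should not wait for a judgement on the observed imbalance.

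**The case against.** The strongest reply is that the rule does not stand alone and that level gaps do limited harm here. Methods/design also removes provinces with distorting local policies. ANCOVA is available for the primary outcome, time series analysis is named, the endpoint is a change, and the planning data showed a ratio of 1. A reader might infer that the significance rule is the only protection of the comparison; the document does not support that. What remains is that neither ANCOVA nor the time series analysis is linked to a check of pre-campaign trends, and that ANCOVA depends on a judgement without a threshold.

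A reader might also infer that the rule passes gaps nearly as large as the target effect. That depends on the chosen inputs. With 500 vs 1500 GPs and SD 6.0 the largest passing gap is 2.9%, close to 3%. But that sample has only about 53% power for 3%, and its 90%-power effect is about 4.8%. A study with 90% power for 3% passes at most 1.8%. At SD 3.0, assumed samples of 500 vs 1500 to 1000 vs 3000 pass only 1.4% to 1.0%.

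Nor does a passing level gap feed directly into the estimate, because a stable gap cancels in a comparison of changes. The percentages above therefore measure the looseness of the rule and are not bias. The document gives no evidence that trends differ between the areas.

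Finally, one might read the rule as choosing control provinces by p-value, with regression to the mean as the result. Methods/design drops provinces for local policies only and describes no selection on the test.

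An article may leave details of trend diagnostics to a fuller document. The significance criterion, however, is stated here as the definition of similarity, so it can be judged as it stands.

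**Conclusion.** The point holds in a limited form. Defining baseline similarity by a non-significant test is unsound: the test accepts level gaps of up to about 60% of whatever effect the study is powered for (1.8% of 21.1 if powered for 3%, 3.0% if for 5%), and its outcome for a given gap turns on the number of GPs and the SD. The 60% rests on two-sided alpha 5%, 90% power, and the same units and SD for the check and the main comparison. It does not rest on any assumed number of GPs.

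The larger weakness is that the rule checks level while the endpoint is a change, so it is silent on parallel pre-campaign trends, the condition that matters most. The size of that problem cannot be worked out from the document. This should be changed, but it does not show that the planned comparison is biased.

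**What to change.** 1. Delete the significance criterion from Methods/design.
2. Fix the list of control provinces before the campaign, on the local-policy criterion alone.
3. Report the baseline difference in prescribing between intervention and control areas with its confidence interval.
4. As a check of parallel trends, compare intervention and control provinces on November-March changes over the earlier seasons available in the regional prescribing databases, with confidence intervals.
5. In Statistical analysis, adjust the primary analysis for baseline prescribing in all cases, instead of only when imbalance is judged relevant.

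The cost is a few lines of text, some extra analysis and one extract from databases the study already uses. This assumes that comparable earlier winters are held for all the provinces concerned, which the document does not say.

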### Study population

The proposed multifaceted intervention will target adult citizens and physicians. Specifically, citizens will be directly targeted by general information through brochures, posters and mass media. General practitioners and paediatricians will receive ad hoc information on antibiotic resistance and will have an active role in facilitating the campaign messages getting through, so that they may be also sensitized to the issue of appropriate antibiotic prescribing (Table 1).

**Table 1 T1:** How the campaign is expected to affect the population targets

		POPULATION TARGETS	
	
		CITIZENS	PHYSICIANS
**LEVEL OF ACTION**	**KNOWLEDGE**	Awareness of the antibiotic resistance issue and of the importance of a correct use of antibiotics (through brochures, posters and mass-media)	Awareness of local data on antibiotic resistance (through a newsletter)
	
	**ATTITUDE**	Awareness that antibiotics are not a panacea, but their use is fundamental in specific circumstances	• Sensitization to the issue of appropriate antibiotic prescribing
			• Perception that patients may be more informed about (and more sensitive to) the antibiotic resistance issue
	
	**BEHAVIOUR**	• Lower pressure on doctors to get antibiotics	Appropriate antibiotic prescribing
		• Less antibiotic self-use	
		• More appropriate use	

